### Ethical considerations

The present study is in accordance with the Helsinki Declaration and the Regulatory Guidelines and Norms for Research Involving Human Subjects of the National Health Board of the Brazilian Health Ministry issued in October 1996. This study received approval from the Human Research Ethics Committee of the Nove de Julho University (Brazil) under process number 329445/2010. Informed consent will be required to all subjects.

All procedures of the study will be confidential. The professional drivers diagnosed for OSA will be referred to the Sleep Medicine service and immediately forwarded to adequate treatment in order to treat the sleep respiratory disorder.

## Discussion

Despite the abundance of scientific evidence, OSA is still underdiagnosed in the general population. This is probably due to multiple causes, such as deficiency of knowledge on the part of physicians and also the limited access of the patients to diagnosis and treatment of OSA [45]. In addition, diagnostic procedures are expensive, and predictive criteria are still unsatisfactory. Obesity parameters are important predictors, although not all OSA patients are obese and not all obese subjects have OSA. The identification of new markers of OSA would be useful.

The aim of the present protocol study is to determine whether the NEP test could be used as a screening tool for OSA and the prevalence of this condition among a population of professional interstate bus drivers. Because increased upper airway collapsibility is one of

the main determinants of OSA [21], the response to the application of NEP could be a predictor of this disorder.

With the enrollment of this study protocol, the expectation is to encounter predictive NEP values for different degrees of OSA. It's a daytime, low-cost screening method that could be included in a preventive strategy in order to contribute toward an early diagnosis of this condition and reduce its impact and complications among professional interstate bus drivers.

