### Objectives

The main objective of the study, which will be conducted on medium and long distance professional interstate bus drivers, is to investigate whether NEP test induced upper airway collapse is indicative for the presence and severity of OSA. Secondary objectives are: 1) identify the prevalence of OSA in this population; 2) determine the prevalence of metabolic syndrome and cardiovascular disease; 3) determine the correlation of work shift on clinical findings; and 4) validate a novel questionnaire on sleep quality proposed by the *Italian National Research Council Institute of Biomedicine and Molecular Immunology "A. Monroy" *and *Centro Medico di Veruno *(Italy).

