### Standard overnight polysomnography

Nocturnal polysomnography will be carried out using the Embla Somnologica Studio - EMBLA A10, version 3.1.2. (Flaga hf. Medical Devices, Iceland) sleep analysis system. The following signals will be recorded: electroencephalogram (F4-M1, C4-M1, O2-M1, and backup electrodes F3, C3, O1 and M2), electrooculograms (E1-M2, E2-M2), chin and tibials electromyography, electrocardiogram, oxygen saturation, pulse rate, oronasal airflow (nasal canula and thermistor), respiratory effort (thoracic and abdominal Xtrace model straps), snoring, and body position. The patients will be instructed to remain relaxed and sleep naturally as at home. Throughout the night, the subjects will be monitored by a technician experienced in polysomnography [42]. The reading will be performed by professionals who were blinded to the result of the NEP test, following the guidelines of the American Academy of Sleep Medicine [43] and criteria of the Brazilian Sleep Society.

Apneas are defined as lack of airflow or a reduction ≥90% in the airflow signal for at least 10 s. Hypopneas are defined as discernible drop in flow by ≥ 30% of baseline for a period lasting at least 10 s followed by a SaO_2 _fall ≥4%. AHI will be calculated as number of (apneas + hypopneas)/h of total sleep time. Subjects with AHI ≥5 will be classified as OSA [42,43].

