### Calculation of sample size and statistical analysis

The calculation of sample size was based on the correlation reported by Insalaco et al. [44] between Δ$\dot{\text{V}}$(%) and AHI in patients with OSA (r = 0.37). For a bidirectional alpha value of 0.05 and 90% power, a minimum number of 82 subjects will be necessary.

Kolmogorov-Smirnov normality test will first be performed in order to determine the presence or absence of a normal distribution sample. Descriptive analysis will be performed, with the data expressed as either mean and standard deviation or median values and 95% confidence intervals, when appropriate. One-way analysis of variance (ANOVA) will be used for comparisons between work shifts once the samples have a normal distribution. V_0.2 _and Δ$\dot{\text{V}}$(%) values will be linearly correlated with the AHI, for which either Pearson's or Spearman's correlation test will be used, depending on the sample distribution. Either the non-paired Student's t-test or Mann-Whitney test will be used for comparisons between individuals with and without OSA. Logistic regression for the analysis of continuous factors with categorical responses will be performed. Receiver operating characteristic (ROC) curves will be constructed to determine the sensitivity (true positive rate) versus 100-specificity (false positive rate) at various levels of the measured Δ$\dot{\text{V}}$ (%) and V_0.2 _(%) to identify the cut-off value yielding the largest number of correctly classified patients. The statistical analysis will be performed by an experienced statistician using the JMP commercial program (version 8.0, SAS Institute Inc.) and SPSS program (version 16.0, Somers NY). A 5% level of significance and 95% confidence interval will be applied.

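### Severity is part of the main objective, but the stated analyses give no NEP value by degree of OSA, and a correlation with AHI in a mixed sample can reflect presence alone

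*Protocol article*

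**What the plan says.** Protocol article, Objectives: the study asks whether "NEP test induced upper airway collapse is indicative for the presence and severity of OSA". Severity therefore belongs to the main objective. The Discussion adds that "the expectation is to encounter predictive NEP values for different degrees of OSA".

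Standard overnight polysomnography gives one threshold: "Subjects with AHI ≥5 will be classified as OSA". The article defines no mild, moderate or severe class.

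Calculation of sample size and statistical analysis lists these analyses:
- Correlation: V0.2 and flow drop "values will be linearly correlated with the AHI, for which either Pearson's or Spearman's correlation test will be used". No analysis set is named. This correlation is also the basis of the sample size (r = 0.37 reported in OSA patients, two-sided alpha 0.05, 90% power, minimum 82).
- A t-test or Mann-Whitney test that "will be used for comparisons between individuals with and without OSA".
- ROC curves that look for one best-classifying cut-off of each NEP index. The AHI threshold that defines a case is not stated.
- Logistic regression with categorical responses that are not named.
- Work shifts: "One-way analysis of variance (ANOVA) will be used for comparisons between work shifts". This is not a split by AHI.

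**The concern.** The objective and the Discussion promise more than the analysis section delivers.

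First, no stated analysis returns a separate NEP value for each degree of OSA. The OSA group test has two groups, the ROC search yields one cut-off per index, and a correlation coefficient is not a cut-off.

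Second, severity rests on the correlation with AHI. The drivers come from a working population and will include many without OSA. If NEP collapse is simply greater in drivers with OSA, with no gradient among them, NEP and AHI still correlate over the whole sample. A report could then say that NEP indicates severity when the data show only that it indicates presence. For a screening test the two claims have different uses: one flags a driver for a sleep study, the other ranks those who have the disease.

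**Working it through.** **The plan's own figure.** Fisher z: n = ((1.960 + 1.282)/atanh(0.37))² + 3, with atanh(0.37) = 0.3884. This gives 72.6, so 73 against the stated 82. The difference is conservative (82 gives 93% power at r = 0.37) and does not bear on this point.

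**Promise against plan.**

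| Promised | Stated analysis | What it yields |
|---|---|---|
| Presence of OSA | Two-group test; ROC | A difference; one cut-off per index |
| Severity | Correlation with AHI | A coefficient, no cut-off |
| Values for different degrees | None stated; no degree defined | No separate value by degree |

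**Can presence alone produce the correlation?**

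Inputs from the article: n = 82 (the stated minimum) and a prevalence p of 28% (Background, professional truck drivers). Assumptions not in the article: the NEP index is normal with SD 1, is shifted by a constant d SD when AHI is 5 or more, and has no relation to AHI within either group.

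Under this model Spearman's rho uses only the ranks of AHI, so the shape of the AHI distribution does not matter. The expected value is approximately

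rho = 6 · p · (1 − p) · (A − 0.5), with A = Φ(d/√2).

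With p = 0.28, 6 · 0.28 · 0.72 = 1.2096.

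| d | A | rho by formula | Mean rho simulated | Whole sample significant | Within OSA significant |
|---|---|---|---|---|---|
| 0.8 | 0.714 | 0.26 | 0.26 | about 66% | about 5% |
| 1.0 | 0.760 | 0.31 | 0.31 | about 83% | about 5% |
| 1.2 | 0.802 | 0.37 | 0.36 | about 92% | about 5% |

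Repeat simulations of 4,000 to 6,000 studies per setting moved the whole-sample percentages by up to about three points. The 5% within OSA is the nominal error rate, as it should be with no gradient. At d = 1.2 the correlation from presence alone is about the size of the r = 0.37 used for planning.

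**What the test within OSA could show at 82 drivers.** Power = Φ(0.3884 · √(m − 3) − 1.960), where m is the number with OSA.
- 28% prevalence: m = 0.28 · 82 ≈ 23, and power = Φ(1.737 − 1.960) = 41%.
- 24.8% prevalence (Background, São Paulo men): m ≈ 20, and power = Φ(1.602 − 1.960) = 36%.

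For 90% power at r = 0.37 within OSA, 73 drivers with OSA are needed. That is 73/0.28 ≈ 261 drivers, or 73/0.248 ≈ 295. Both are below the 710 to be invited.

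**The case against.** Severity is not ignored. The correlation uses AHI as a continuous measure, is the analysis that the study was sized on, and takes its planning value from patients with OSA. The article does not name the analysis set, so the authors may intend to run it within OSA. The objective itself promises no cut-offs by band; that expectation appears only in the Discussion. Bands and subset analyses are often left to a fuller document. The simulated step at AHI 5 with no gradient is an assumption, and 82 is a minimum.

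Much of this stands, and it rules out stronger readings. A reader might infer that every group comparison and every ROC curve splits at AHI 5. The article does not say so: the ANOVA compares work shifts, the ROC reference is not stated (AHI of 5 or more is merely the only candidate), and the logistic responses are unnamed and could include severity classes. A reader might also infer that the plan yields no NEP value for any degree. That goes too far, because a cut-off at AHI 5 is a value for OSA of any degree.

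What does not fall is the mismatch within the article. It states a severity objective and an expectation by degree, defines one class, and describes a correlation without the restriction that would separate severity from presence. Leaving detail to another document does not reconcile those statements.

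**Conclusion.** The point holds as a cheap improvement. The analyses as stated do not match the expectation of NEP values for different degrees of OSA, and the correlation, if run on all drivers, cannot by itself support a severity claim. At 82 drivers, 28% prevalence and a constant shift of 0.8 to 1.2 SD, presence alone gives rho of about 0.26 to 0.36 and significance in about 66% to 92% of studies, against about 5% within OSA.

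The shift, the step at AHI 5 and the use of truck-driver prevalence are assumptions. The Background gives no AHI threshold for the 28%. The figures show that the plan can mislead in this way, not that it will. A reader might infer that the correlation tells nothing about severity. The documents do not support that: it addresses severity in part, and would isolate it if run within drivers with OSA.

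**What to change.** In Calculation of sample size and statistical analysis:

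(a) Add the correlation of each NEP index with AHI among drivers with AHI of 5 or more. Report it with a 95% CI beside the whole-sample correlation, and base any statement on severity on it.

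(b) Either add ROC curves with AUC, sensitivity, specificity and 95% CIs at higher AHI bands that the sponsor fixes before analysis, or limit the conclusion, and the expectation in the Discussion, to presence of OSA. The article gives no higher bands, so the choice is the sponsor's. Fixing them beforehand prevents choosing them after seeing the data.

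The cost is a few sentences and extra runs on data already collected. The downside is low precision if enrolment stays near 82: about 20 to 23 drivers with OSA, power of about 36% to 41% for r = 0.37 within OSA, and fewer drivers still in any higher band. A non-significant result within OSA should then be reported as inconclusive, not as evidence that NEP is unrelated to severity.
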